***Secondary outcomes***

 Clinical frailty status measured by CFS at three months after the start of intervention. Muscle mass measured by bioelectrical impedance at three months after the start of intervention.Body fat, bone weight, base metabolic rate, biological age by bioelectrical impedance at three months after the start of intervention. Incidence of in-patient hospitalisation during follow-up. Incidence of long-term care admission (LTC) during follow-up. Ease of the intervention measured on a five-point scale: ‘very easy’, ‘somewhat easy’, ‘neither easy nor hard’, ‘somewhat hard’, or ‘very hard’ three months after the start of intervention. Difference to general health as a result of the exercises measured on a five-point scale: ‘much better’, ‘slightly better’, ‘about the same’, ‘slightly worse’ or ‘much worse’ three months after the start of intervention.

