### Study methods, assessments and procedures

GP site investigators will undergo three team-based training sessions prior to enrolment, monthly meetings after enrolment and additional ad-hoc meetings when required, led by the principal investigator, in order to standardise the approach and align to this study protocol, including patient communication, intervention delivery and data gathering and management.

Adults attending a GP surgery, meeting the eligibility criteria, will be offered general information about the study by the attending GP. If interested and willing to consent, they will be offered an information leaflet for the trial, and invited to participate. Participants will be randomly assigned to ‘intervention’ or ‘usual care’ parallel arms.

Participants randomly assigned to the usual care group will receive normal primary care, including physical rehabilitation if needed.

Intervention participants will be provided a leaflet with strength exercises and a discussion on how strength exercises have been shown to delay and reverse frailty and build resilience. The information leaflet will have a photographic overview of a home-based exercise regime. They will also be provided with information on post exercise protein consumption as part of a normal balanced diet.

Baseline measurements for all recruited patients will be: age, sex, education, living arrangement (alone, with others), smoking status, alcohol intake, blood pressure, heart rate, BMI (weight and height), comorbidities, malnutrition universal screening tool (MUST), CFS, SHARE-FI (which includes handgrip strength) and bioelectrical impedance for muscle mass, body fat, bone weight, base metabolic rate and ‘biological age’. Bioelectrical impedance will be measured using a Tanita RD 545 Segmental Body Composition Analyser, with dual frequency technology and medical grade accuracy.

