Intervention participants will be called after one month and after three months by the GP and asked if they had followed the exercise regime (and for how long and how many times a week) and dietary guidance. At three months they will be asked if they found the exercises ‘very easy’, ‘somewhat easy’, ‘neither easy nor hard’, ‘somewhat hard’, or ‘very hard’; and had they noticed any subjective difference to their health as a result of the intervention, namely feeling ‘much better’, ‘slightly better’, ‘about the same’, ‘slightly worse’ or ‘much worse’. All participants will be invited to return at three months for a clinical assessment and measurement of health indicators and frailty status as described above by the GP. Participants will be invited to return for subsequent one year follow up appointments. This 12-month follow up will be subject to a further ethics committee review. The follow up visits will be free of charge. A schedule of events for baseline, one-month call and three months follow up are shown in
Figure 3.

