### Efficacy analysis

Efficacy analysis will be performed on all primary and secondary efficacy endpoints. Point estimates, interval estimates (95% confidence interval) and p-values will be reported.

***Primary efficacy endpoint*.** The primary outcome is Frailty status measured by SHARE-FI at three months of follow-up.

Changes in proportions in non-frail, pre-frail and frail categories will be analysed in both study arms and reported as an odds ratio with associated 95% confidence intervals and tested for significance using a standard chi-square test of proportions.

We hypothesise that participants on resistance exercise regime and with guidance on dietary protein will have a higher SHARE-FI score than patients without this intervention.

This outcome will be analysed as a difference in means between treatment arms using a linear mixed effects model, with arm allocation, SHARE-FI at baseline and age included as fixed effects and GP practice included as a random effect.

***Secondary efficacy endpoints*.** Clinical frailty status measured by CFS at three months will be analysed using a proportional odds mixed model with arm allocation and age as fixed effects and GP practice as random effect. Muscle mass measured by bioelectrical impedance at three months will be analysed using a logistic mixed model with arm allocation as fixed effect and GP practice as random effect.

Ease of the intervention measured on a five-point scale and difference to general health as a result of the exercises measured on a five-point scale will be analysed using a proportional odds model with arm allocation as covariate.

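### Ease of the intervention and perceived health change are asked of intervention participants only, yet both are to be modelled with an arm effect that one-arm data cannot estimate

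*Protocol article*

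**What the plan says.** Under Secondary outcomes the protocol lists two participant-reported items at three months: "Ease of the intervention measured on a five-point scale" and "Difference to general health as a result of the exercises measured on a five-point scale".

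Under Study methods, assessments and procedures it says how they are collected. "Intervention participants will be called after one month and after three months by the GP". The text goes on: "At three months they will be asked if they found the exercises" easy or hard, and "had they noticed any subjective difference to their health as a result of the intervention". The same section then turns to both arms: "All participants will be invited to return at three months for a clinical assessment and measurement of health indicators and frailty status". Neither five-point item is named in that sentence. For the control arm it says: "Participants randomly assigned to the usual care group will receive normal primary care, including physical rehabilitation if needed". The exercise leaflet, the discussion and the protein information are described for the intervention arm alone.

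Under Efficacy analysis both items "will be analysed using a proportional odds model with arm allocation as covariate". Arm is the only covariate named. The opening of that section promises an estimate, a 95% confidence interval and a p-value for every primary and secondary efficacy endpoint.

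**The concern.** The collection plan and the analysis plan do not fit together. The analysis presumes responses from two arms, and the collection text provides them from one. A regression coefficient for arm needs respondents in both arms.

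At stake is a pre-specified analysis of two secondary outcomes that cannot be carried out as written. These are the two outcomes that serve the secondary objective. The analyst would have to replace the model after the data are in. The protocol's section on deviations from the statistical plan requires any such change to be reported to the ethics committee and approval sought. It is cleaner to correct the text beforehand.

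**Working it through.** **Inputs from the protocol**

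- Allocation 1:1 by simple randomisation (Randomisation).
- 176 evaluable and 210 enrolled, 15% dropout, 15% versus 3% improving to non-frail, type I error 0.05, power 80% (Determination of sample size).
- Model: proportional odds with arm as covariate (Efficacy analysis).
- Feasibility ratings of ease: 32%, 55%, 7%, 6% and 0% from easiest to hardest (Feasibility study). They serve only as a plausible response distribution.

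**Step 1. The plan's own sample size**

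The protocol gives no figure for the two five-point items, so its only sample size is checked first. Sidedness is not stated; two-sided is assumed. With pooled variance and no continuity correction,

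n per arm = [1.960 × √(2 × 0.09 × 0.91) + 0.842 × √(0.15 × 0.85 + 0.03 × 0.97)]² / 0.12² = 88.1, rounded up to 89, or 178 in total.

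The protocol's 176 (88 per arm) has power 79.96%, so the figure is reproduced to within rounding. For dropout, 176 / 0.85 = 207.1 (208) and 178 / 0.85 = 209.4 (210), which agrees with 210. Expected numbers per arm are therefore 176 / 2 = 88 evaluable and 210 / 2 = 105 enrolled. Simple randomisation makes these approximate.

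**Step 2. Who supplies the two items**

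| Item | Intervention arm | Usual-care arm |
|---|---|---|
| Ease | asked at three months | not named; no study exercises to rate |
| Health change | asked at three months | not named; wording attributes change to the exercises or intervention |
| Clinical assessment, health indicators, frailty status | yes | yes |

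**Step 3. What the planned model can estimate**

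The model is logit P(Y ≤ k | x) = θₖ − βx, with x = 1 for intervention and 0 for usual care. If every respondent has x = 1, the likelihood depends only on the differences θₖ − β. Adding any constant c to all θₖ and to β leaves it unchanged, so β is not identified.

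A numerical check used the feasibility distribution. The hardest category is empty there, which leaves four categories, three thresholds and one arm term: four parameters.

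| Respondents (intervention, control) | Rank of information matrix | Eigenvalues |
|---|---|---|
| 88, 0 | 3 of 4 | 0 (to rounding), 7.46, 24.46, 38.94 |
| 88, 88 | 4 of 4 | 4.56, 15.17, 45.48, 53.05 |

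With one arm the matrix is singular. The result does not depend on the response distribution or on the number of respondents.

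**Step 4. What one-arm data do support**

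Category proportions can be estimated. In the worst case, p = 0.5, the half-width of a 95% interval by the normal approximation is 1.96 × √(0.25 / 88) = 0.104 with 88 respondents and 1.96 × √(0.25 / 105) = 0.096 with 105. That is about ±10 percentage points.

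**The case against.** Several points can fairly be made for the plan.

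- **The schedule of events might show controls being asked.** Figure 3 was not available for this check, so a control-arm entry cannot be ruled out. The text does not say that controls attend for nothing else. However, such an entry would sit badly with the Study methods text. It would not rescue the ease item, since controls have nothing to rate, and the health item would ask controls to attribute change to exercises they were not given. The caveat matters mainly for the health item.
- **The error reveals itself.** A model with a constant arm column returns no arm odds ratio, so it cannot produce a false claim of benefit. This stands, and it limits the severity.
- **The detail could be left to the statistical analysis plan.** The protocol does not leave the model open. It names one that does not match the data to be collected.

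Three stronger readings are tempting, and the documents do not support them.

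- *The secondary objective cannot be met.* That objective concerns participants' views on ease and on personal health benefit. It names no comparison between arms and can be met descriptively from the intervention arm.
- *Imputation will invent control answers.* The missing-data section limits chained equations to cases where imputation is appropriate, and nothing directs that these items be imputed in controls. With no control responses, the method would also have nothing from which to learn the contrast.
- *A control response would separate benefit from expectation.* Participants know whether they received the leaflet and the discussion. A self-rating asked in both arms would give an estimable contrast but would still mix the two.

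**Conclusion.** The inconsistency is real and narrow. On the protocol's text, both items are collected in the intervention arm only, and the arm effect in the stated model is not estimable. If controls were asked after all, the ease contrast would be meaningless and the health contrast, as worded, hard to interpret.

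The effect is limited to two secondary outcomes. The primary outcome, the sample size, the other secondary outcomes and the safety analysis do not depend on it. It should be corrected, but it does not threaten the trial's main conclusion.

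The conclusion rests on reading the people asked at three months as the intervention participants of the preceding sentence, and on Figure 3 not saying otherwise. The figures of about 88 and about 105 assume equal arms and the protocol's 15% dropout.

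**What to change.** 1. In Efficacy analysis, delete the arm covariate for both items. Report the proportion in each category with a 95% confidence interval in the intervention arm, with the number who answered (about 88 expected, up to about 105).
2. State that the two items are not applicable in the usual-care arm and are not imputed there.
3. Check that Figure 3 agrees with the Study methods text on who is asked.

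These are wording changes. They need no new data and no change in sample size, and they go through the ethics submission that the protocol prescribes for modifications.

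*Optional.* If a between-arm comparison of perceived health is wanted, put a neutrally worded general-health item, with no reference to the exercises, to both arms at the three-month visit that all participants are already invited to attend, and analyse that item by arm. Keep the attributed item as description in the intervention arm. The costs are an ethics committee amendment that changes data collection, one extra question, and a new outcome to list. Its result would still carry expectation bias, because it is an unblinded self-rating. The decision has to be made before the three-month visits, since answers not collected then cannot be recovered.

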### Safety analysis

Incidence of in-patient hospitalisation during follow-up and incidence of LTC during follow up will be analysed using a logistic regression model with arm allocation and age as covariates.

All non-serious and serious AEs will be reported in tables in aggregate form by frequency and subjects affected by trial arm.

### The level of statistical significance

For hypothesis testing the significance level will be set at 0.05.

### Procedure for accounting for missing, unused and spurious data

Where appropriate, missing data will be imputed using multivariate imputation by chained equations (van Buuren & Groothuis-Oudshoorn, 2011).

### Procedure for reporting any deviation(s) from the original statistical plan

Deviation(s) from the original statistical plan will be reported in writing to the research ethics committee and approval sought.

## Retention of essential documents

All records and documents will be maintained by the principal investigator for a period of 12 months after the end of the trial.

## Ethics

### Declaration of Helsinki

The supervisor will ensure that this study is conducted in accordance with the ethical principles that have their origins in the Declaration of Helsinki.

### Good clinical practice

This study will be conducted in accordance with Good Clinical Practice, as defined by the International Conference on Harmonisation (ICH) and in accordance with the ethical principles underlying European Union Directive 2001/20/EC and 2005/28/EC.

### Approvals

Ethical approval has been granted by the research ethics committee of the Irish College of General Practitioners on November 3, 2020

Approval for protocol modifications or amendments will be sought through formal REC submission and communicated to stakeholders (e.g., investigators, REC/IRBs, trial participants, trial registries, journals) by email where appropriate or by phone to participants with consent.

### Informed consent

The GP will take informed consent in the primary care consultation. Informed consent will be obtained prior to any study related procedures being undertaken. The GP will explain the nature of the study to the participant, and answer all questions regarding this study. Prior to any study-related screening procedures being performed, the informed consent statement will be reviewed and signed and dated by the participant and the GP.

A model consent form is available at the Harvard Dataverse repository
^22^.

### Subject confidentiality

The trial staff will ensure that the participants’ anonymity is maintained. The participants will be identified only by first names and identification number on any database. All documents will be stored securely. The study will comply with the Data Protection Act.

### Data management committee

In line with guidance from the European Medicines Agency, an external data management committee will not be part of this trial, due to the short time frame, non-critical nature of the syndrome being addressed and low risk of harm from the intervention.

## Insurance/Indemnity

The GPs hold medical liability insurance as required by the Irish College of General Practitioners and the Medical Council.

## Dissemination

Initial dissemination of results will be through publication in a peer reviewed journal. The study team will also work with advocacy, primary care and academic partners to disseminate the findings. These will include, Age Action, the Irish College of General practitioners, University College Dublin and Trinity College Dublin. The study is at an early stage and is due to commence enrolment in December 2020. However, early planning for dissemination is underway and agreement for same received from the Health Research Board Primary Care Clinical Trials Network.

## Data availability

### Underlying data

All data underlying the results are available as part of the article and no additional source data are required.

### Extended data

Harvard Dataverse: Reversing Frailty and Enhancing Resilience (REFEREE) RCT.
https://doi.org/10.7910/DVN/RKEGIV
^22^.

This project contains a model consent form used in this study.

### Reporting guidelines

Harvard Dataverse: SPIRIT checklist for ‘Protocol for a randomised controlled trial of a primary care intervention to Reverse Frailty and Enhance Resilience through Exercise and dietary protein Education (REFEREE) in community-dwelling adults aged 65 and over’.
https://doi.org/10.7910/DVN/TCOCSV
^23^.

Data are available under the terms of the
Creative Commons Attribution 4.0 International license (CC-BY 4.0).
